#### Statistical methods

Analyses will be performed on the intention-to-treat (ITT) population including all randomized participants analyzed according to the randomization scheme. Due to the lack of data (HRQoL) studies, a sub-population will be defined for the analysis of HRQoL, corresponding to a modified ITT population, i.e., all ITT patients with at least the available HRQoL score at baseline.

Qualitative variables will be described using frequency and percentage distributions. The number of missing data will be given, but will not be considered for the calculation of proportions.

Quantitative data will be described using the number of observations, mean, standard deviation, median, minimum and maximum values.

For the primary endpoint analysis, the time to definitive deterioration (TTD) will be defined as the time interval since randomization to the observation of the first deterioration (decrease for global HRQoL score and increase for fatigue score) of 5 points at least as compared to the baseline score, with no further improvement of 5 points at least as compared to the baseline score [49, 64]. Patients with no deterioration observed during the study will be censored at the time of the last available score. Patients with no follow-up score will be censored 1 day after their inclusion. If a deterioration is followed by missing data, this deterioration will be considered as definitive. TTD will be estimated using the Kaplan-Meier method and compared between groups with a log-rank test, stratified by the presence of visceral metastases, the method of administration of chemotherapy and the 6MWD, at a two-sided significance level of 0.04 (TTD1) or 0.01 (TTD2). Univariate and multivariate Cox regression models will be performed to explore factors influencing the TTD.

Sensitivity analysis will be performed to assess 10-point deterioration in global HRQoL score and fatigue in comparison with baseline. Sensitivity analysis will also be performed including death as an event.

An analysis of missing data profile at baseline and during follow-up will be performed in order to determine the missing data profile. The responders versus non-responders for HRQoL questionnaire at baseline will be compared according to clinical and socio-demographics variables collected at baseline in order to determine a potential missing at random profile (i.e. missing data depending on observable variables). To investigate a potential missing not at random profile (i.e. missing data depending on non-observable HRQoL level), these profiles of participants (responders vs. non responders at baseline) will be compared according to the overall survival. A graphical analysis of HRQoL data over time until drop out will be performed in order to explore a potential missing not at random profile for missing data during follow-up.

Multiple imputations could be explored for baseline missing HRQoL data, taking into account the variables linked to the occurrence of baseline missing HRQoL data and HRQoL analyses will be repeated then after as sensibility analyses.

For secondary endpoints analysis, progression-free survival will be measured from the date of randomization until the date of event defined as the first documented progression or death from any cause. Participants with no event at the time of the analysis will be censored at the date of the last available tumor assessment. Overall survival and progression-free survival will be estimated using the Kaplan-Meier method and will be described in terms of median progression-free survival per arm, and hazard ratio for progression between the two arms. Associated 2-sided 95% confidence intervals for the estimates will be provided.

Change from baseline will be compared between the two arms: secondary HRQoL dimensions, multidimensional dimensions of fatigue, physical fitness, anthropometric measurements, PA level, sleep disorders, sarcopenia, chemotherapy toxicities, inflammation and oxidative stress, personality factor and process of change regarding PA.

The proportion of refusal (number of participants who refused to participate in the study / number of participants to whom the study was proposed) will be calculated.

Statistical analyses will be performed using SAS® software version 9.4 or later.

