**Methods:**

ABLE02 is a prospective, national, multicenter, randomized, controlled and open-label study. A total of 244 patients with a metastatic breast cancer, with at least one positive hormone receptor and a first-line chemotherapy planned, will be randomly assigned (1:1 ratio) to: (i) the intervention arm to receive physical activity recommendations, an activity tracker to wear 24 h a day during the whole intervention (6 months) with at least three weekly walking sessions and quizzes each week on physical activity and nutrition (ii) the control arm to receive physical activity recommendations only. Health-related quality of life will be assessed every 6 weeks and main assessments will be conducted at baseline, M3, M6, M12 and M18 to evaluate the clinical, physical, biological and psychological parameters and survival of participants. All questionnaires will be completed on a dedicated application.

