### Evaluations

#### Modalities

All patients will benefit from four face-to-face assessments, when attending the participating hospital center for their regular oncology follow-up visit:an initial assessment at inclusion before the start of the first line of chemotherapy (or up to 1 month after the start of chemotherapy) (Baseline), a second assessment 3 months after inclusion (halfway through the intervention) (M3), a third assessment 6 months after inclusion (i.e., at the end of the intervention) (M6) and a fourth assessment 12 months after inclusion (6 months after the end of the intervention) (M12). During these face-to-face assessments, a PA instructor will perform the physical assessments and the anthropometric measurements and a blood sample will be taken. In case of first tumour progression during the study, an additional blood sample will be taken.

All participants will also have to complete questionnaires directly via the mobile application or on the website “ABLE02” every 6 weeks until W24 and then every 12 weeks until W48 (Inclusion, W6, W12, W18, W24, W36, W48) and then 18 months after inclusion. At each time point, the participant will be notified that a new questionnaire is available and must be completed. If a participant does not complete a questionnaire, a second notification will be sent 1 week after the initial notification. Participants encountering difficulties to fill in a questionnaire have possibility to contact the clinical research assistant. Questionnaires not completed by a participant will be automatically deleted after 6 weeks. The clinical research assistant will track questionnaire completion via the ABLE02 professional dashboard to limit missing data and will have the possibility to enter directly questionnaire data collected by phone or face-to-face via the internet dashboard to help patients who meet difficulties.

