### Data collection

A complete data collection schedule is provided in Table 1.

**Table 1 Tab1:** Data collection schedule for the ABLE02 study

	Inclusion +/- 7d	W6 +/- 7d	M3/W12 +/- 15d	W18 +/- 7d	M6/W24 +/- 21d	M9/W36 +/- 21d	M12/W48 +/- 1M	M18 +/- 1M	Progression

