#### Demographic and clinical data

Demographic data, including, living situation, employment status, education, socio-professional level, and distance from the cancer center will be collected by auto-questionnaire at inclusion and will be filed out in an electronical case report form (e-CRF). Clinical data and date of birth will be collected from the participant’s electronic medical record and will include date of diagnosis, hormonal status, tumor histology, personal history of breast cancer at inclusion, current treatment, sites of metastases and Response Evaluation Criteria In Solid Tumors (RECIST). All adverse events of grade 3 and above, whether related to the intervention or not, will be collected.

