#### Skeletal muscle and sarcopenia

Skeletal muscle and sarcopenia will be assessed based on CT scans, performed routinely in all breast cancer patients. A cross-sectional CT image at the midpoint of the third lumbar vertebrae (L3) will be extracted from CT scan for each patient at each time and analysed using the National Institutes of Health (NIH) ImageJ software [56]. The cross-sectional area (mm^2^) of the seven muscles of the L3 region (psoas, rector spinae, quadratus lumborum, transversus abdominus, external and internal obliques and rectus abdominus) will be evaluated by measuring the area composed by all pixels having an attenuation comprises between − 29 and + 150 Hounsfield units (HU) excluding those located within internal cavity [57, 58]. Skeletal muscle density (SMD) (HU) represents the mean attenuation of these pixels. Skeletal muscle index (SMI) (cm^2^/m^2^) will be obtained by normalizing the cross-sectional muscle area by patient stature. Skeletal muscle area at L3 was shown to predict whole lean body mass (LBM) according to the following equation [59]:
$$ LBM(kg)=0.3\times cross\;\mathit{\sec} tional\kern0.17em muscle\kern0.17em area\; at\;L3\left({cm}^2\right)+6.06 $$

Participants will be considered as sarcopenic if they have an SMI <40cm^2^/m^2^ and participants will be considered to have a poor muscle quality if they have SMD < 37.8HU [60] .

Images will be transferred to the coordinating center. Then, two technicians or physicians will be in charge of a double reading - blind to the study arm allocated to participants - to determine the sarcopenic status of participants.

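### PFS counts events with no cut-off, but tumour status of event-free women is scheduled only to M12; unless later scans are recorded, the late PFS curve, late medians and a non-null hazard ratio are biased

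*Protocol article*

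**What the plan says.** All references are to the protocol article.

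- **Events.** Under Statistical methods, PFS runs from randomization to the "date of event defined as the first documented progression or death from any cause". No date is given after which events stop counting.
- **Censoring.** "Participants with no event at the time of the analysis will be censored at the date of the last available tumor assessment".
- **Reporting.** "Overall survival and progression-free survival will be estimated using the Kaplan-Meier method", with medians, a hazard ratio and 95% confidence intervals. No test or alpha is attached to PFS.
- **Collection.** Under Data collection: "A complete data collection schedule is provided in Table 1". That table marks CT at inclusion, M3, M6, M12 and progression. It marks clinical data at inclusion, M3, M6, M9, M12 and progression, and at M18 for survival only. The M12 window is ± 1 month. The section Demographic and clinical data lists RECIST among the clinical data taken from the medical record.
- **Progression.** Table 1 has a Progression column, and Modalities adds: "In case of first tumour progression during the study, an additional blood sample will be taken".
- **Source of the scans.** Under Skeletal muscle and sarcopenia, that assessment is "based on CT scans, performed routinely in all breast cancer patients".

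**The concern.** Take two women who are event-free at M12. One dies or has a documented progression at month 15 and enters the analysis as an event at month 15. The other is alive and progression-free at M18, but if nothing after M12 is on file about her tumour, she is censored back near M12. Whether a woman counts as at risk between M12 and M18 then depends on whether she later has an event. Kaplan-Meier and Cox both assume that this is not so.

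PFS stands, with overall survival, first in the list of secondary aims. Its median per arm and hazard ratio are what readers will take from it, and a curve that falls steeply after M12 for reasons of data collection would be read as disease behaviour.

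**Working it through.** **Plan's own figures.** The article gives no median, event count or power for PFS, so there is no PFS figure to reproduce. The co-primary event count does reproduce: 4 × (2.054 + 1.282)² / (ln 0.615)² = 44.52 / 0.2363 = 188.4, so 189. It does not depend on this point.

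**Inputs.** 122 women per arm (244 at 1:1); M12 window ± 1 month (Table 1); survival collected to M18 (Table 1). Assumed: exponential PFS; control median 6, 8, 10 or 13 months; hazard ratio 1 or 0.615 (the latter borrowed from the TTD1 design); all events to M18 captured; no tumour assessment after M12 on file for event-free women.

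**Step 1: closed form, with censoring at exactly M12.** Let S(t) = 0.5^(t/m) for median m. Women event-free at 18 months, a fraction S(18), are all censored at 12. For 12 < t ≤ 18 the risk set is S(t) − S(18), so

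KM(t) = S(12) × [S(t) − S(18)] / [S(12) − S(18)].

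- At t = 18 this is zero for any S, given the stated condition.
- m = 8: KM(15) = 0.354 × (0.273 − 0.210) / (0.354 − 0.210) = about 0.15, against a true 0.27.
- m = 10 / 0.615 = 16.26: S(12) = 0.600 and S(18) = 0.464. KM = 0.5 requires S(t) = 0.464 + 0.5 × (0.600 − 0.464) / 0.600 = 0.577, so t = 16.26 × log₂(1/0.577) = about 12.9 months, against a true 16.3.

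**Step 2: simulation with the visit window** (censoring uniform on M11 to M13, 400 replicates, true hazard ratio 0.615).

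| Control median (assumed) | HR, rule with no later scan | HR, status known at M18 | HR, both cut at M12 assessment | Intervention median: true → rule | True PFS at M18, control / intervention |
|---|---|---|---|---|---|
| 6 | 0.653 | 0.615 | 0.614 | 9.8 → 9.7 | 0.125 / 0.278 |
| 8 | 0.663 | 0.608 | 0.612 | 13.0 → 12.5 | 0.210 / 0.383 |
| 10 | 0.658 | 0.608 | 0.604 | 16.3 → 13.3 | 0.287 / 0.464 |
| 13 | 0.681 | 0.618 | 0.619 | 21.1 → 13.7 | 0.383 / 0.554 |

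Under the rule, Kaplan-Meier at M18 was zero in both arms in every replicate. At M11 it was still correct (0.387 against a true 0.386, control median 8). With a true hazard ratio of 1 the rule gave 0.99 to 1.01.

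**Step 3: some later scans on file.** Control median 10, hazard ratio 0.615, 5,000 per arm, half of the women event-free at M18 having a recorded scan at months 15 to 18. Kaplan-Meier at month 17 was 0.23 against 0.31 (control) and 0.39 against 0.48 (intervention). The intervention median was 14.6 against 16.4. The hazard ratio was 0.635, nearly unbiased.

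**Step 4: shift against precision.** At control median 8, on average 25.4 and 47.1 women are event-free at M18, so events = 244 − 72.5 = 171.5 and SE(log HR) is about √(4/171.5) = 0.153. The shift is ln(0.663/0.608) = 0.087, or 0.57 of a standard error.

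**The case against.** The strongest reply is that the article never says that the last available tumour assessment is the last one in Table 1. Scans are routine care and RECIST comes from the medical record, so later scans may be in the chart, and any that is recorded keeps an event-free woman at risk past M12. Table 1's M18 column is not exhaustive either: Modalities asks for questionnaires 18 months after inclusion, and the table marks none there. The abstract says that "main assessments will be conducted at baseline, M3, M6, M12 and M18", and survival at M18 could be meant to include progression status. That progressions count up to M18 is inferred from the Progression column; only deaths are clearly collected to then. The full protocol or case report form may already hold the scan date.

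Much of this stands. A reader might infer that both PFS curves must fall to zero by M18 whatever the truth. The documents do not support that: it needs no recorded assessment after M12 and, in each arm, at least one event after the last censoring time. Nor is censoring at the last tumour assessment a faulty rule in itself; it is standard.

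What does not stand is that the point is mere missing detail. The event rule, the censoring rule and the schedule are all stated, and followed as written they make follow-up after M12 depend on outcome. The abstract's mention of M18 names no tumour assessment. Partial capture of later scans largely repairs the hazard ratio, but not the tail of the curve or the late medians (Step 3).

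**Conclusion.** The concern holds conditionally and should be settled before the PFS analysis. If tumour status after M12 is not recorded for event-free women, PFS is biased downward from about M11 on, reaching about zero by M18 with no later scan on file and falling less far with some. Medians beyond about 12 months are pulled down, and a true hazard ratio of 0.615 moves to about 0.66 to 0.68 for assumed control medians of 8 to 13 months. That shift is modest, roughly half a standard error in this trial, and runs toward 1. It does not create a false effect, since a null hazard ratio stays at about 1. The larger harm is to the curves and late medians.

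The sizes rest on assumed exponential medians and on full capture of events to M18; the article gives no PFS figure. If the control median is short (6 months), both medians survive intact and only the tail and the hazard ratio are affected. The co-primary analyses and the sample size are not touched.

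**What to change.** Choose one and state it in the PFS definition.

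(a) At M18, record from the chart, for every woman without progression, her progression status and the date of her last routine tumour assessment, and censor there. Amend the M18 clinical-data cell of Table 1 to match. Cost: two chart-derived fields at a time point that already exists, and no extra scan. It is easiest while follow-up is open. Last scans will often precede M18 by some weeks, so the end of the curve still needs cautious reading; the recovery shown in Step 2 assumes status known at M18 itself.

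(b) If nothing more can be collected, set one PFS cut-off at the M12 assessment (with its window) for both events and censoring, so that later progressions and deaths do not count as PFS events. Cost: one sentence, fewer PFS events, and no estimable median beyond 12 months.

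Under either option overall survival stays followed to M18. If the full protocol or case report form already records the last assessment date at M18, saying so and correcting Table 1 is enough.

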### Data monitoring

The randomization and database for clinical data will be created using EnnovClinical® software and the access will be secured (personal ID and password required) with different levels of security depending on the role of the investigator. All questionnaires will be completed on a dedicated application ABLE02 and merge to the clinical database at the end of the study. Data monitoring will be provided by the trial steering committee, including overall project supervision, progress monitoring, advice on scientific credibility and ensuring the integrity and appropriate running of the project. The clinical research assistant will verify all consent forms, compliance with established protocol and procedures, and data quality in the eCRF and thanks to the ABLE02 professional dashboard every month. The research team will make quarterly reports to the trial steering committee.

### Dissemination

Only one guideline for patients with bone metastasis has brought to light the need to continue an active lifestyle as long as possible but still few patients have incorporated these recommendations for fear of injury and worsening their health condition [65]. The development of a smartphone application linked to an activity tracker allows remote patient monitoring and could be a good solution to replicate in clinical practice. Findings of the ABLE02 trial will be disseminated via peerreviewed publications and conference presentations.

## Discussion

Unlike localized breast cancer, only few studies in PA have been conducted in MBC despite participants’ willingness to participate in programs [15, 17, 20, 66–68]. A meta-analysis of randomized controlled trials in participants with advanced cancers, including only three studies in metastatic breast cancer, showed that supervised aerobic or resistance interventions could be beneficial for physical fitness and sleep quality, but data remained controversial concerning HRQoL, fatigue and body composition [17]. Further efficacy studies are needed in this population to highlight the benefits of PA for participants with MBC and to determine the optimal type, intensity, frequency and duration of PA program.

Patients with MBC are a specific population with significant functional limitations and needs [6, 7, 14, 69]. A large majority of the ABLE Trial participants were interested (89%) and felt able (93%) to participate at moderate intensity in a walking PA program designed specifically for patients with MBC [68]. Moreover, the high recruitment (94%) and adherence rates (96%) suggest the willingness of patients with MBC to participate in PA program [20]. The growth of e-health allows to overcome different geographic, financial and organizational barriers and to still propose semi-supervised adapted PA interventions to a larger population [32, 70]. Cancer participants’ interviewed also indicated that they found activity tracker useful to monitor and increase their PA [24, 25, 67].

Patient empowerment is an effective approach to help people to gain control over their lives, to increase their capacity to act, to manage their illness and side effects of treatment and to become autonomous [71, 72]. Patient empowerment may also improve their well-being, emotional state and reduce the need for supportive care and health costs [71]. New approaches, using connected devices such as web platforms, make it possible to facilitate patient access to their own data, to personalized information and also obtain real-time data with patient feedback. Activity trackers are part of the paradigm shift from the medical model to the global model and constitute innovative means, vectors of the therapeutic alliance, which allow an improvement of health literacy of individuals for a long-term prevention strategy. They contribute to the autonomy and emancipation of users in their care process. To promote PA by changing behaviors and lifestyles, it is essential to empower the patients to influence his or her health. Previous studies have found that chronic illness, such as cancer, are associated with detrimental personality changes [73, 74], it seems to be crucial to find interventions that can counterbalance such changes. If prior studies have found PA may prevent maladaptive personality development among people without chronic disease [75, 76], no study has investigated the extent to which PA for patients with MBC may be associated with personality change. ABLE02 study will be the first to test the effect of PA interventions on personality traits development among MBC patients.

The balance between protein synthesis and degradation is finely controlled in skeletal muscle by numerous cell signaling pathways and the molecular regulators upstream such as the autophagy-lysosome and ubiquitin-proteasome systems, the IGF-1/Akt/mTOR pathway, the Smad2/3 pathway, inflammatory cytokines, myostatin or glucocorticoids [77–79]. Oxidative stress has also been shown to be involved in the etiology of cancer-associated sarcopenia [80]. In addition, circulating mediator of oxidative stress could characterize early sarcopenia in patients with lung cancer [81]. Finally, in an animal model of colon cancer, regular PA suggested to reduce the phenomenon of sarcopenia by reducing oxidative stress [82]. However, no study of these biomarkers has been performed in MBC after PA intervention. The results of the ABLE02 study will investigate several signaling pathways to show an effect of PA on biological parameters.

Finally, the impact of the physical activity on the immune status of the patient will also be monitored (lymphocytes counts, activation status, plasma cytokines). Indeed previous works from the clinician team has reported the major impact of the lymphopenic status on breast cancer patient outcome from first line metastatic chemotherapy.

Finally, the impact of the physical activity on the immune status of the patient will also be monitored (lymphocytes counts, activation status, plasma cytokines). Indeed previous works from the clinician team has reported the major impact of the lymphopenic status on breast cancer patient outcome from first line metastatic chemotherapy [83–85]. Immunotherapy approaches are starting to demonstrate benefit in breast cancer patients (ref AMM atezo in TNBC), thus the recovery of better immune status following PA will represent a strong argument to combine immunotherapy with PA programs in the objective to increase response rate.

The ABLE02 trial was based on the promising results of the ABLE single-arm trial, which highlighted the interest of patients with MBC in participating in PA interventions but also an improvement in physical fitness as well as maintenance of muscle mass, quality of life and fatigue despite the progress of the disease [20, 42]. The ABLE02 trial is the first study to test the efficacy of a PA program based on connected devices (smartphone application and activity tracker) to improve HRQoL and reduce fatigue in women with MBC and to assess the effect of an intervention on other biological, psychological and functional parameters.

